### Aims and objectives

The primary clinical aim of PtC is to describe patterns of short and long-term persistence (as measured over 7 months and 18 months respectively) across three HIV PrEP products, individually and overall, amongst a cohort of South African adolescents and youth. Participants are offered a choice between PrEP products, following HIV testing and comprehensive choice counselling. PrEP products include (a) oral PrEP (Emtricitabine/tenofovir), prescribed as a daily tablet or for event-driven use for select male participants; (b) a Dapivirine-containing vaginal ring (DapiRing) that requires monthly replacement, for non-pregnant and non-breastfeeding adolescent girls and young women; and (c) Cabotegravir long-acting (CAB-LA) as a two monthly intra-muscular gluteal injection.

PrEP persistence is defined as sustained, continuous use of the selected product as intended, with consideration of both (a) a < 7-day gap in PrEP availability for daily dosing (oral PrEP), DapiRing insertion, or subsequent injection or (b) a < 28-day gap. The 7-day gap between the scheduled return vs. actual return is consistent with the definitions used in CAB-LA phase 3 clinical trials [17]. – [18] The 28-day gap follows South African recommendation guidelines for a “missed visit” and is the clinical time point where re-initiation on CAB-LA would be needed. In the South African context, it is expected that the 28 day gap will provide a more realistic timeframe for return. In addition to a missed visit, non-persistence on a specific product is further defined as any participant that switches to using another PrEP product with (a) < 7 days and (b) < 28-day gap between products. PrEP persistence in the cohort, by product and on PrEP overall, will be calculated and reported at 7 months (short-term persistence) and 18 months (long term persistence). The comparison of PrEP persistence by product will be related to the hypothesis that there will be a significantly greater persistence in the CAB LA group compared to oral PrEP and/or DapiRing.

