The primary implementation aim is to determine what combination of implementation strategies best achieve PrEP adoption (decision to use any PrEP product), active implementation (PrEP initiation), and persistence (sustained PrEP use) outcomes within a RE-AIM (Reach, Effectiveness, Adoption, Implementation, Maintenance) implementation science framework. This will be assessed over the short term (7 months) and long term (18 months), considering barriers and enablers for both the PrEP user and PrEP provider. Mixed qualitative and quantitative methods and process evaluations will be used to inform the implementation analysis.

Several secondary aims and an exploratory aim are described in Table 1.

**Table 1 Tab1:** An overview of PtC study primary and secondary aims, including their endpoints and time of measurement

Aim	Endpoint (s)	Time of measurement
*Primary Aims*		
1.1 To compare short term persistence (over 7 months) across PrEP modalities and PrEP overall (*Clinical aim)*	Persistence - defined as sustained, continuous use of the selected PrEP product as intended, with consideration of both (a) a < 7 day gap or (b) a < 28 day gap in PrEP provision for daily dosing (oral PrEP), DapiRing insertion, or subsequent injection. Participants that product switch are considered *PrEP persistent overall* but not *PrEP product persistent*. Product use patterns, including product switches and re-starts, are tracked for the full 7-month period for all persistent and non-persistent participants.	7 months from PrEP initiation.

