1.2 To determine what combination of implementation strategies best achieve PrEP adoption and persistence over the short term within a RE-AIM framework (*Implementation aim).*	*Reach* – (i) time to recruit the injectable PrEP study population (*n* = 900 participants); (ii) demographic and clinical characteristics of PrEP initiators vs. persistent users vs. non-persistent users in each PrEP product user group. *Effectiveness* – (i) frequency and description of PrEP product reported side effects; (ii) frequency and description of reported social harms, including intimate partner violence. *Adoption* – (i) proportion of participants reached and sustained at mobile clinic vs. government facilities; (ii) frequency, timing, and nature of product switches and PrEP discontinuation, informed by a qualitative assessment of reasons for non-persistence. *Implementation* – (i) description and evaluation of PrEP choice counselling delivery as per counselling time per person, fidelity assessment scores, and correlation of documented counselling outcomes with actual PrEP persistence; (ii) Evaluation of injectable PrEP administration according to clinical operating procedures. *Sustainability* – (i) sustainability of PrEP choice delivery at participating sites as assessed through the clinical sustainability assessment tool and (ii) qualitative assessment of acceptability and readiness to receive future long-acting PrEP products.	All participants having passed through (a) 7 months and (b) 18 months of study participation.
*Secondary Aims*		
2.1 To compare long term persistence (over 18 months) across PrEP modalities and PrEP overall (*Clinical aim)*	As above for aim 1.1.	18 months from PrEP initiation.
2.2 Time on PrEP based on expected (injections given; product collected) vs. actual (self-reported patterns of use) PrEP coverage *(Clinical aim*)	Total time on PrEP overall based on oral/vaginal PrEP collection and injections vs. self-reported patterns of use. Actual time and self-reported time on PrEP for injectable PrEP users is equivalent.	7 months and 18 months from PrEP initiation.

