#### Statistical analysis

PrEP initiation in this study is defined as having received a 28-day regimen of oral PrEP tablets, receiving a DapiRing, or receiving a CAB-LA injection depending on the respective product choice. Initiators are participants that have selected a specific PrEP product at baseline after receiving PrEP choice counselling.

To determine the primary and secondary endpoints of short-term and durable persistence (as defined above), a Cox proportional hazards model to estimate the hazard of discontinuing PrEP at 7 months and through 18 months will be conducted, thus taking into account the presence of censoring due to end of study period or drop-out, including all participants who are confirmed as HIV-uninfected at enrolment and who attend at least the PrEP initiation visit (visit 1).

More specifically, PrEP persistence at 7 and 18 months will be summarized in the first instance as proportions of subjects on a given modality at those time points out of those who started on the modality and compared using a chi-square test. Additionally, Kaplan-Meier curves will illustrate the time to discontinuation by PrEP modality. Cox proportional hazards model will be used to analyse the risk of discontinuation overall, (i) regardless of modality and (ii) taking modality into account. Frailty models will account for repeated discontinuations per subject. Modality will be included as a time-varying exposure variable. Additionally, time to switching modality will be analysed using a Cox proportional hazards model, with frailty terms to account for repeated switches, if required. Models will include subject-specific characteristics that may confound the association between modality and risk of discontinuation. Different subgroups (adolescent girls and young women, intimate male partners, and gay and other men who have sex with men) can be included as a predictor in the models and additionally analysis will be repeated for sub-groups of interest. The average time to restart, the mean number of restarts for a participant and the total number of restarts across the study period will be reported and used to describe the variation in PrEP user journeys throughout the product.

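### Restart is summarised by a plain average time, which is biased short when some who stop have not restarted by the end of follow-up; a time-to-event summary should replace it (minor, descriptive output)

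*Protocol article*

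**What the plan says.** The Statistical analysis section names three restart summaries: "The average time to restart, the mean number of restarts for a participant and the total number of restarts across the study period". Their purpose is descriptive; they "will be reported and used to describe the variation in PrEP user journeys throughout the product". The section gives no denominator, at-risk set or censoring rule for them, and announces no test and no contrast between products for restart.

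The other two processes in that section are treated differently. Discontinuation has Kaplan-Meier curves and a Cox model, "thus taking into account the presence of censoring due to end of study period or drop-out". For switching, "time to switching modality will be analysed using a Cox proportional hazards model", with frailty terms if required.

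Table 1 (Aims and objectives) fixes how long a restart can be observed. Under aim 1.1, "Product use patterns, including product switches and re-starts, are tracked for the full 7-month period for all persistent and non-persistent participants". Long-term persistence under aim 2.1 is measured at "18 months from PrEP initiation".

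**The concern.** A restart can happen only after a stop, and is seen only if it falls before the participant drops out or follow-up ends. Someone who stops and has not restarted by then has no restart time to average. A plain average therefore keeps the quick restarts and loses the slow ones and the absent ones, and no value can exceed the follow-up left after stopping.

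The mean number of restarts raises a separate point of interpretation. If the denominator is all participants, the figure depends on how many stop and when, as well as on how readily those who stop come back. The protocol expects persistence to differ by product: its hypothesis is that "there will be a significantly greater persistence in the CAB LA group compared to oral PrEP and/or DapiRing". Numbers stopping should then differ too, and so would restarts per participant, even with the same tendency to restart.

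At stake is how time off PrEP is described to those planning delivery. The persistence comparison itself is untouched.

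**Working it through.** The document states no restart figure, so there is none to reproduce. The check asks what a plain average of observed restarts would show under known truths.

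**Inputs from the document.** Horizons of 7 and 18 months from initiation (Table 1).

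**Assumptions, since the document gives no rates.** Exponential restart times with true mean M of 1 to 12 months; exponential time on product with mean 3, 6, 12 or 24 months; no drop-out; the same restart rate in every group.

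**Step 1: closed form for a fixed stopping time.** With W = horizon minus stopping time, the mean among observed restarts is

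E[T | T < W] = M - W·exp(-W/M) / (1 - exp(-W/M)).

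For M = 6 and the 18-month horizon:
- Stop at month 4: W = 14 and exp(-14/6) = 0.0970, so 6 - 14 × 0.0970/0.9030 = 4.50 months.
- Stop at month 12: W = 6 and exp(-1) = 0.3679, so 6 - 6 × 0.3679/0.6321 = 2.51 months.

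For M = 1 the same two stops give 1.00 and 0.99 months, almost no bias.

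**Step 2: simulation of alternating on and off periods** (200,000 participants per scenario). Observed mean time to restart in months, for mean time on product of 3/6/12/24 months:

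| True mean | 18-month horizon | Shortfall | 7-month horizon | Shortfall |
|---|---|---|---|---|
| 1 | 0.94 in all four | about 6% | about 0.84 | about 16% |
| 3 | 2.46/2.44/2.42/2.43 | 18-19% | 1.67/1.64/1.61/1.59 | 44-47% |
| 6 | 3.93/3.85/3.77/3.71 | 35-38% | 2.10/2.01/1.99/1.95 | 65-68% |
| 12 | 5.36/5.12/4.92/4.82 | 55-60% | 2.37/2.26/2.21/2.15 | 80-82% |

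Shortfall is 1 - observed/true; for example, 1 - 3.93/6 = 35%. Down each column the bias depends strongly on the restart rate. Along each row, across groups that differ only in how quickly they stop, it hardly moves.

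**Step 3: when some never restart.** If half of those who stop never restart and the others have a mean of 6 months, the observed average at 18 months is still 3.8-4.3 months. The plain average does not show the half who never return.

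**Step 4: number of restarts** (true mean 6, 18 months, mean time on product 3/6/12/24 months):
- per participant: 1.78/1.25/0.78/0.44, a ratio of 1.78/0.44 = 4.0;
- per participant who stopped: 1.78/1.32/1.01/0.84;
- per person-month off PrEP, counting unrestarted time: 0.166-0.167 in every group, against a true 1/6 = 0.167.

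Only the last measure recovers the common restart rate.

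**The case against.** The strongest reply is that the text is silent rather than wrong. This is a condensed article, and an analysis plan that is not shown could set denominators and censoring. A Kaplan-Meier median or restricted mean is, loosely, also an average. This stands in part: the document nowhere says that censoring will be ignored. But it names the summary, and it names time-to-event methods for the two sibling processes in the same section. Followed as written, the average runs over observed restarts.

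Second, restarts may be quick. Discontinuation can be a gap of only 7 days, participants are contacted after 7 days without a return, and the Discussion expects a 28-day window to improve the rate of return. If the true mean is near 1 month, the bias at 18 months is about 6%. This stands as a limit on size. It is less reassuring under the 28-day definition, where returns within 28 days are not discontinuations at all; the origin from which time off is counted is not stated.

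Third, restarts per participant is a legitimate burden measure, and fewer restarts on a more persistent product is a true description. This stands; the fault would lie only in reading it as a restart rate.

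Fourth, aim 2.2 in Table 1 separately reports total time on PrEP, so time off PrEP is not judged from restarts alone. This also stands and limits the consequence.

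**Conclusion.** The point holds as a minor one. A plain average time to restart, taken over observed restarts, is biased short. Under exponential restart without drop-out, the shortfall over 18 months is about 6% for a true mean of 1 month and about 35-38% for 6 months. It is larger over 7 months, if the average is also reported then; the text speaks only of the study period. The document cannot say which case applies.

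Two stronger readings are tempting and not supported:
- **That restart will look much faster than it is.** This is one scenario among several, and depends on a slow restart rate that no figure in the document establishes.
- **That average time to restart will differ between products through stopping time alone.** When only discontinuation rates differ, the spread is small (3.9 against 3.7 months at 18 months with a true mean of 6). It becomes large only if stopping times differ sharply, as in 4.5 against 2.5 months for stops at months 4 and 12. The protocol announces no comparison of restart by product.

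The count per participant can differ fourfold at an identical restart rate. That calls for care in interpretation and does not make the measure wrong. No primary or secondary endpoint depends on these summaries.

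**What to change.** Replace the plain average with a Kaplan-Meier or cumulative-incidence estimate of time from discontinuation to restart:
- include all who discontinue, with numbers at risk;
- censor at drop-out or end of follow-up, and treat seroconversion as a competing or censoring event, stating which;
- state the time origin, and produce the estimate for each gap definition (7 and 28 days);
- report the proportion restarted by fixed times, such as 3 and 6 months after stopping;
- report restarts per person-month off PrEP beside the raw mean and total, and state the denominator of the mean.

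The cost is about a sentence of analysis text and no new data, since Table 1 already tracks restarts in persistent and non-persistent participants. The restart figures will probably look less favourable. The estimate also assumes that those lost after stopping restart like those still followed, which should be said when it is reported.

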## Discussion

The PtC study is evaluating the real-world implementation of PrEP choice, with the first-time inclusion of three approved PrEP products. The protocol was specifically designed to simulate a realistic context for PrEP roll-out, with the aim to firstly, evaluate persistence with expanded PrEP choice and secondly, describe practical challenges that may occur when recruiting young people into HIV prevention services, providing PrEP choice counselling, initiating PrEP, and supporting PrEP continuation.

These aims are supported by the inclusion of two types of settings, mobile clinics and primary health care facilities. Mobile clinics are capable of reaching participants in community spaces (such as malls, sports grounds, and transport hubs), offer a tailored and efficient health services, and can be designed to be adolescent friendly. These attributes partially overcome some of the well-described challenges of primary health care clinics [21]. However, mobile services in this study are also staffed by teams that may be better resourced (in terms of staff, equipment, and support) and more familiar with research than in clinic settings. This may falsely elevate PrEP outcomes in this setting, compared to a more traditional government setting. The government primary health care facilities are small clinics with limited resources and staffing, that provide a limited primary care service that includes SRH and HIV treatment and care. Some of the barriers to services in this environment have been reported to include long waiting times, unfriendly staff attitudes, high staff turnover, and medication stock outs [1, 3]. However, the vast majority of PrEP choice in SA will be delivered from such facilities which therefore provide a realistic view of PrEP implementation challenges.

PtC has purposefully included a broad population range of adolescent and young people, including heterosexual males and gender and sexually diverse populations, rather than tailoring the service to adolescent girls and young women (a traditional PrEP target in the Eastern/Southern African setting). This was pursued intentionally to firstly, reduce stigma that can arise from only offering PrEP to a single population designated to be high risk, and secondly, to allow for a description of natural PrEP uptake rates among different populations when offered as a generalised service to young people. The resulting data will be used to inform which populations can be accessed through generalised services and which populations may need dedicated outreach interventions and spaces. Where possible, peer navigators from sexual and gender diverse groups have been employed.

The introduction of injectable PrEP, CAB-LA, has been broadly anticipated to alter the PrEP landscape, increasing both uptake and persistence. However, CAB-LA use up until this point has only been described in the context of clinical trials where robust eligibility criteria, study reimbursement, and strict visit schedules likely influenced the rate of on time return for subsequent injections. On time return in these studies was described as within a 7-day window [17, 18]. In the South African context, this is broadly considered to be unrealistic due to several factors including participant challenges with transport, inflexible work schedules, and community safety concerns. It is hypothesized that a more flexible 28-day visit window is likely to allow an improved rate of return and persistence, while still operating within the bounds of clinical safety and PrEP product efficacy. The PtC study as such will report on persistence using both a 7 day and 28-day visit window to highlight the impact of this on reported persistence outcomes.

A primary focus of this study will be to develop a feasible and acceptable means of PrEP choice counselling delivery that ensures accurate information while supporting the agency of the individual PrEP user. One challenge is that choice counselling will occur in a busy clinic environment necessitating a rapid and easy to use strategy. Another challenge is the concise and accurate communication of new and unfamiliar concepts with newer PrEP products, such as the long duration of injectable PrEP and the association with antiretroviral drug resistance or the placement, comfort, and daily impact of having a DapiRing in situ.

## Limitations

This study has several limitations. Firstly, while an extensive effort will be made to simulate real-world conditions, there are some aspects of the clinical trial setting that cannot be avoided. This includes oversight from highly qualified and trained study staff members that may offer a higher level of specialized care than what is provided in public healthcare settings where staff turnover may be high. PtC staff members are specifically trained in adolescent and youth friendly service provision and will undergo gender sensitization training, which is not necessarily part of standard of care training packages. Secondly, the PtC counselling intervention assumes the continuous availability of an experienced HIV counsellor, which is not always the case in primary healthcare settings where counsellors may also often see high staff turnover. Thirdly, the mobile clinic and government primary health clinic site are likely to have notable differences including the number of study support staff and the focus of the service, with the mobiles offering a targeted SRH service and the clinic supporting multiple diverse primary care services. Outcomes that may be influenced by these differences will be formally tested for in the study analysis.

## Conclusion

South Africa benefits from being one the first countries to receive regulatory approval of and access to all currently available PrEP products. HIV prevention services, including HIV testing and counselling and oral PrEP provision, is already well-integrated into primary health care with antiretroviral-based medication (including treatment and PrEP) prescribed by trained and accredited primary care nurses. There is broad public awareness of HIV, with appreciation for the high HIV prevalence and incidence and increasing general interest in HIV prevention services. Yet, oral PrEP has been available in SA for more than a decade, and although SA has been a leader in numbers of new PrEP users in 2024, initial implementation was hindered by slow roll-out and lower than expected uptake and persistence. PtC is an implementation project that will contribute to understanding how implementing PrEP choice may enhance uptake and effective use. This will inform future efforts to implement PrEP choice rapidly, safely, and at a scale sufficient to drive down HIV transmission in South Africa.

## Data Availability

No datasets were generated or analysed during the current study.
